### Withdrawal and dropout

2.9

If any subject withdraws consent, is found to be in violation of the inclusion and exclusion criteria, etc., or if the PI judges that continuing participation of the subject in this study is inappropriate, he or she will be dropped from this study. The researchers will record whether each subject participating in this study completed it or not, as well as the reason for any interruption in the intervention.

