### Sample size calculation

2.3

Based on the results of a pilot study and clinical significance, we assume that the mean difference (δ) between the changes in the VAS before and after treatment in each group is 15 and the standard deviation (σ) is 24.71. When a significance level of 5%, a power of 90%, and an assignment ratio of the groups of 1:1 are applied, the number of subjects in each group (n) is given by^[14]^ 

Also, for an expected dropout rate of 20%, according to 

at least 73 subjects per group are required, for a total of 146 subjects.

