#### Cointerventions

2.5.3

All subjects will be instructed not to receive any treatment for back and/or leg pain, except for the treatments we provide. During the period of participation in the clinical trial, they will receive rescue medication (i.e., acetaminophen, up to 3000 mg per day). They will be instructed to take the rescue medicine only when their back and/or leg pain is so severe that it is unbearable. At each visit, the clinical research coordinator (CRC) will accurately record on the CRF the total rescue medication dosage used by the subject since the last visit.

At the discretion of the researching physician, all subjects will be allowed to continue to take medications that they were taking before their participation in this study. The subjects will be instructed to report to the researcher at each visit any changes in the dosages of the medications that they have been taking or any new medications that they have taken since they began participating in this study. They will also be instructed not to take arbitrarily a drug that might affect the study's outcomes. If the subject does not follow the above instructions and if the principal investigator (PI) judges that those actions could significantly influence the study's outcomes, that subject will be dropped from this study.

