### Adverse events

2.7

In this study, all undesirable medical findings in which symptoms were not observed until participation in this clinical study will be classified as AEs. The researchers will carry out an AE assessment at each visit based on vital signs, history taking, and other test results. In addition, the subjects will be instructed to report voluntarily any adverse situations to the researchers at every visit, and the researcher will confirm such reports through medical examination. All identified AEs will be recorded on the CRF, regardless of their association with acupotomy treatment or manual acupuncture treatment. The researchers will assess the severity of the AE and take appropriate action. If serious adverse events (SAEs) occur, such as a life-threatening event or disorder or any other medically important condition, the PI should decide whether or not the subject should be dropped from this study.

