### Statistical analysis

2.8

The data obtained from the subjects of this study will be analyzed in the form of a full analysis set (FAS) analysis group and a per protocol (PP) analysis group. The FAS analysis group refers to analyzing a set of subjects that minimizes those who are excluded, except for a legitimate reason, from the analysis among the randomly assigned subjects. The PP analysis group refers to analyzing a set of subjects who have participated in more than 75% of the interventions (3 or more interventions) specified in this study's protocol and have not violated this study's protocol, and for whom the assessment variables have been measured completely. Both the FAS analysis group and the PP analysis group will be used for the effectiveness analysis while the main analysis group will be the FAS analysis group and the auxiliary confirmation will be performed by using the PP analysis group.

All statistical analyses will be conducted using the 2-tailed test in principle, and the significance level will be set at 5%. Analyses will use the statistical program SAS Version 9.4 (SAS Institute, Inc, Cary, NC). When missing values are encountered, they will be processed using multiple imputations.

The descriptive statistics of the subjects’ demographic characteristics and clinical baseline variables, such as gender, age, history, and drug dosage, will be presented for each treatment group. If the comparisons between the 2 groups involve continuous data, the mean and the standard deviation will be presented, and analyses will be performed using the independent *t* test or the Wilcoxon rank sum test. As needed, the 95% confidence interval will be provided. If the comparisons between the 2 groups involve categorical data, the frequency and the percentile will be presented, and analyses will be performed using the chi-square test or the Fisher exact test.

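### Patients can be dropped from the study after randomisation on the PI's judgement without securing their 4-week VAS, and FAS exclusions are left open, so the main analysis may depart from intention-to-treat

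*Protocol article*

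**What the plan says.** Three sections of the protocol article end participation in the study, not only the intervention:

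- **2.9 Withdrawal and dropout.** Besides withdrawal of consent and a breach of the eligibility criteria (an open list), "if the PI judges that continuing participation of the subject in this study is inappropriate, he or she will be dropped from this study".
- **2.5.3 Cointerventions.** If a patient disregards the instructions on other treatment and drugs, and the PI judges that this could significantly influence the outcomes, "that subject will be dropped from this study".
- **2.7 Adverse events.** After a serious adverse event, "the PI should decide whether or not the subject should be dropped from this study".

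Section 2.8 makes the full analysis set (FAS) the main set and describes it as "a set of subjects that minimizes those who are excluded, except for a legitimate reason, from the analysis among the randomly assigned subjects". It does not say what counts as a legitimate reason. Missing values are to be multiply imputed. The per-protocol (PP) set is auxiliary and requires "more than 75% of the interventions (3 or more interventions"), no protocol violation and complete assessments.

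The four interventions take place over 2 weeks (2.2), and the primary outcome is the VAS change at 4 weeks after randomisation (2.6). Patients and treating clinicians cannot be blinded (2.4).

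**The concern.** Stopping a treatment and leaving a trial are different events, and the article uses one word for both. After the fourth intervention there is no study treatment left to stop, yet the co-treatment rule still runs. A drop between then and week 4 therefore mainly removes the primary outcome.

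The loss could well depend on outcome. The trigger in 2.5.3 is itself the likely effect on the outcomes, and it is plausible (though the article does not say so) that patients whose pain persists are the ones who look for other treatment. The rates could also differ by arm, because patients and clinicians know the allocation and the decision is a judgement. If poor responders leave one arm more often than the other, the primary comparison is biased. An analysis plan written later cannot recover outcomes that were never collected.

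**Working it through.** **1. The plan's own figure.** Inputs from 2.3: "the mean difference (δ) between the changes in the VAS before and after treatment in each group is 15" (mm), "the standard deviation (σ) is 24.71", and "a significance level of 5%, a power of 90%, and an assignment ratio of the groups of 1:1 are applied". Tests are two-sided (2.8).

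n = 2 × [24.71 × (1.960 + 1.282) / 15]² = 57.03, rounded up to 58 per group. With 20% dropout, 58 / 0.80 = 72.5, rounded up to 73 per group, 146 in total. This reproduces the stated size.

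Power is 90.5% with 58 per group and 95.6% with all 73. The planned losses, 73 − 58 = 15 per group, are covered for power. The issue is bias.

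**2. What happens to a dropped patient.**

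| Question | What the article says |
|---|---|
| Are the later visits (2, 4 or 6 weeks) still made? | Not stated; the patient is dropped from the study |
| Does the patient stay in the FAS? | Not stated; exclusions are minimised, with an unspecified exception |
| If kept, how is the missing VAS handled? | Multiple imputation |
| Is the PI blinded? | Not clear; 2.4 lists assessors, data collectors and statisticians, and says that researchers will not know the intervention |

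**3. Size of the possible bias.** Let a fraction p of one arm be dropped, with mean improvement d mm smaller than in the patients kept. The mean of those kept exceeds the mean of the whole arm by

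bias = p × d.

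The article gives neither p nor d. Assumed: p = 5% or 10% in one arm only, d = 10, 20 or 30 mm.

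| p | d = 10 | d = 20 | d = 30 |
|---|---|---|---|
| 5% | 0.5 mm | 1.0 mm | 1.5 mm |
| 10% | 1.0 mm | 2.0 mm | 3.0 mm |

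Against 15 mm this is 0.5/15 = 3% to 3.0/15 = 20%. If the whole 20% dropout allowance were of this kind in one arm, the same formula gives 2 to 6 mm. If both arms lose patients, the bias is the difference between the two products, so balanced loss largely cancels. If d = 0 there is none.

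**4. Consequence for the test.** With 73 per group the standard error of the difference is 24.71 × √(2/73) = 4.09 mm. With no true effect, the chance of a significant result is about Φ(b/SE − 1.96) + Φ(−b/SE − 1.96). That is about 5.2% for b = 0.5 mm and about 11% for b = 3.0 mm.

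**5. Imputation.** Imputation within arm from observed data removes the part of d that those data explain, for example baseline VAS, 2-week VAS if measured, and recorded rescue use. What remains is p times the unexplained part of d. Under missing-at-random that remainder is taken to be zero, which is the doubtful assumption when the reason for the drop is linked to later pain.

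**6. PP threshold.** 3/4 = 75.0% exactly. A patient with three of the four interventions meets the parenthesis and fails the percentage.

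**The case against.** The strongest reply is that the article does not say what a critical reader might infer from it.

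- **The FAS.** A reader might infer that dropped patients leave the FAS, or that any reason suffices. The text says that exclusions are minimised, which is conventional near-intention-to-treat wording. It never ties being dropped to removal from the FAS, and compliance is a criterion for the PP set only. This stands: departure from intention-to-treat is possible, not established.
- **Follow-up.** That the 4-week VAS is not collected after a drop is a natural reading, but it is not stated. A full protocol or analysis plan may say more. This stands in part. The drop rules themselves are written here, and as written they take the patient out of the study.
- **The PI.** A reader might infer that the PI is unblinded. The text leaves this unclear.
- **Co-treatment.** The rule needs both disregard of instructions and a judged significant influence, and rescue medication gives persistent pain a permitted outlet. Both may keep such drops few.
- **Safety.** A reader might infer that patients dropped after a serious adverse event leave safety follow-up. The article does not say so, and 2.8 lists all adverse events and records all serious ones.
- **Size and direction.** The bias figures rest on assumed values, and loss of poor responders from the control arm would work against acupotomy.

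The replies do not remove the core: patients can be dropped from the study on judgement after randomisation, with nothing shown that secures their primary outcome.

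**Conclusion.** The point holds as a risk created by the wording. The drop rules do not separate stopping the intervention from ending follow-up, and the permitted FAS exclusions are open. The main analysis may therefore depart from intention-to-treat, and primary outcomes may be lost selectively. The documents do not support the stronger statements that the analysis is not intention-to-treat or that data will be lost selectively.

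The size is unknown. On the one-arm assumptions above it is 0.5 to 3.0 mm, from negligible to material beside 15 mm. It favours acupotomy if poor responders are lost from that arm and counts against it if they are lost from the control arm.

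This should be fixed before analysis, and early enough that outcomes can still be collected. The PP threshold is a separate, minor contradiction that affects only the auxiliary set.

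**What to change.** 1. In 2.5.3, 2.7 and 2.9, separate stopping the intervention from leaving the study. State that a protocol deviation, prohibited co-treatment, an eligibility breach found later or a serious adverse event does not by itself end data collection. The clinical grounds for stopping treatment stay as they are and are not judged here.
2. Collect the 2-, 4- and 6-week assessments and adverse events for all randomised patients unless consent to follow-up is withdrawn.
3. In 2.8, define the FAS as all randomised patients, analysed as randomised, with no exclusion for compliance or for events after randomisation.
4. Have deviations for the PP set classified by someone blinded to arm.
5. Separately, write the PP rule as *at least 75% (3 or more of 4)*.

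The cost is protocol wording and an instruction to both sites. The visits are already scheduled and the sample size stays at 73 per group. The downside is slightly more variable outcomes from non-compliant patients.

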### Ethics and monitoring

2.10

This study is designed based on the Helsinki Declaration and the Korean Clinical Practice Guidelines and has been approved by the Korean Institutional Review Board of DUDKMH (number DJDSKH-18-BM-02). This study protocol is registered with the Korean National Clinical Research Information Service (WHO) (CRIS-KCT0002824). All subjects participating in this study may withdraw their consent at any time for any reason and may discontinue their participation on a voluntary basis.

The data and records related to the conduct of the clinical research will be maintained in separate places at DUDKMH and Daejeon University Cheonan Korean Medicine Hospital. At the completion of the study, independent researchers will edit, classify, and code data for statistical analyses. The monitoring of data and research performances will be conducted regularly by researchers from the Korea Institute of Oriental Medicine. The results of this study will be published in a peer-reviewed paper.

## Discussion

3

This study is designed to compare the clinical effectiveness of acupotomy treatment with that of manual acupuncture treatment for patients suffering from lower back or leg pain due to LDH. Reductions in pain and dysfunction and increases in lumbar mobility and quality of life will be evaluated to confirm whether the subjects with LDH had improved or not. In addition, a safety assessment will be conducted by examining any adverse events that might occur in any of the participants in this study.

LDH may cause back and/or leg pain due to physical stress on the herniated area, chemical (inflammatory) stimuli, microcirculatory circulation disturbance, edema of the nerve root region, and the like.^[32,33]^ As shown in other studies, acupotomy treatment is effective in reducing back and/or leg pain because it relieves chronic adhesions and blood flow disturbances around the nerve by using a needle thicker than that of manual acupuncture to stimulate strongly the local area.^[16,34]^ The authors of this study have applied acupotomy treatment to patients with a variety of vertebral diseases and have published a number of case reports^[10–12]^ and a pilot study.^[14]^ The results of the pilot study confirmed, to some extent, the clinical effectiveness and safety of the acupotomy treatment, but the study had some limitations. First, it was a single center study. Second, patients in the acupotomy group received a lidocaine injection before acupotomy treatment and a wet-cupping treatment after acupotomy treatment, but patients in the manual acupuncture group did not. This is because the pilot study compared the 2 acupuncture treatments in the same manner as they are used in clinical practice. Finally, the pilot study had only 1 follow-up assessment, which occurred at 4 weeks after randomization. Therefore, to minimize these limitations, we designed this study as a large-scale, multicenter study. In addition, neither lidocaine injections nor wet-cupping treatments were used in either group. This is because this study will compare 2 acupuncture treatments in such a way that the numbers and frequencies of those treatments are the same; only the stimulation method is different. When the acupotomy needle is inserted, however, the pain at the treated site is so severe that the skin at that site needs to be anesthetized; in this study, only lidocaine cream was used for that purpose. In addition, for longer and more accurate observation, this study includes 2 follow-up assessments, 1 at 4 weeks and the other at 6 weeks after randomization.

This study has some strengths. The researchers diagnose the LDH of the subjects by using comprehensive judgments based on radiologic examination (CT or MRI), physical examination, clinical symptoms (back and/or leg pain), medical opinion of the clinician, etc., and then judge whether or not he/she can participate in this study. In addition, blood tests and history taking, which are conducted at the screening visit, can be used to exclude subjects with hemostatic disorders, which should prevent SAEs that may occur as a result of the acupotomy treatment.

This study, however, also has some weaknesses. The results are examined up to 6 weeks after randomization (6W), which is still a rather short follow-up period. Also, some differences may exist between the 2 groups in the treatment method of intervention (e.g., treated site, depth of needle insertion, total amount of stimulation, etc.). Because the procedures of the 2 interventions are so different, neither the practitioner nor the patients could be blinded, and the presence of nonspecific variables (e.g., expectation of the subject about the clinicians and the interventions of this study, the subject's expectation on the alleviation of the symptoms through the acupotomy treatment, threshold of pain, etc.) cannot be excluded. Nevertheless, because of the multicenter RCT design of this study, the results are expected to provide useful information for confirming the effectiveness of acupotomy for the treatment of patients with LDH symptoms. Furthermore, the results are expected to confirm that acupotomy treatment for such patients is as safe as manual acupuncture treatment.

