### Objective

2.1

In this multicenter, randomized, controlled, assessor-blinded, clinical trial, we will evaluate the effectiveness and safety of acupotomy for treating back and/or leg pain in patients with LDH. The objectives of this clinical trial are twofold: to compare the pain intensity on the visual analog scale (VAS) in the acupotomy group with that in the manual acupuncture group at 4 weeks after randomization and to investigate adverse events (AE) that occur during the study.

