The primary outcome variable is the mean changes in the score on the VAS at 4W compared with the baseline and will be analyzed using an analysis of covariance with the covariates being the VAS score at baseline and the fixed factor that in each treatment group. Secondary outcome variables will be analyzed in the same manner as the primary outcome variable. If the outcome variables are categorical data, they will be analyzed using the chi-square test or the Fisher exact test. If necessary, a paired *t* test or Wilcoxon signed-rank test will be used for the primary and the secondary outcome variables to analyze differences in measured values before and after treatment in each group, and a repeated measures analysis of variance will be performed to test the difference in the trend at each visit. The Dunnett procedure will be used for multiple comparisons.

If necessary, subgroup analyses of outcome variables, such as demographic variables measured at baseline (e.g., gender, age, duration of illness, treatment expectancy, etc.), whether or not rescue medicines were taken, the amounts of rescue medications taken, the hospital at which the subject was treated, etc., may be conducted. The safety assessments will primarily be performed by analyzing the frequency of adverse events and SAEs that the researchers suspect to be associated with treatment. The collected safety data will be appropriately summarized. All adverse events that occur will be listed with a detailed description. All SAEs will be recorded descriptively. Adverse events will be collected through patient symptom reports and researcher observations. The frequency of each adverse event associated or not associated with intervention will be recorded and analyzed using descriptive statistics. No interim analysis will be performed.

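### The Discussion expects the trial to confirm equal safety, but the article sets no safety margin or comparative criterion, plans descriptive adverse event frequencies and sizes the trial on VAS alone

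*Protocol article*

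**What the plan says.** The last sentence of the Discussion (section 3) states that "the results are expected to confirm that acupotomy treatment for such patients is as safe as manual acupuncture treatment". The Introduction reports the pilot in the same terms, with acupotomy found to match manual acupuncture on safety, and says the present trial is meant to confirm effectiveness and safety.

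The methods sections are more modest:

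- **Section 2.1, Objective.** The safety aim is "to investigate adverse events (AE) that occur during the study".
- **Section 2.8, Statistical analysis.** "The safety assessments will primarily be performed by analyzing the frequency of adverse events and SAEs that the researchers suspect to be associated with treatment". Then: "The frequency of each adverse event associated or not associated with intervention will be recorded and analyzed using descriptive statistics". Adverse events are also to be listed and serious ones described.
- **Section 2.3, Sample size calculation.** The only driver is pain: "we assume that the mean difference (δ) between the changes in the VAS before and after treatment in each group is 15". The SD used is 24.71, and the calculation takes 5% significance, 90% power and equal allocation. After a 20% dropout allowance this gives 73 per group.

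The article states no expected adverse event rate, no safety margin and no comparative safety hypothesis.

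**The concern.** To say that one treatment is as safe as a named comparator is to say that any excess harm is smaller than some tolerable amount. Confirming that needs the tolerable amount to be fixed beforehand and an interval for the between-arm difference to be set against it. Neither is stated, so there is no criterion by which the announced conclusion could be met or missed.

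The sentence matters because it sets in advance how the safety results are expected to be read, and the Introduction shows that the same conclusion was already drawn from the pilot. Nor do the interventions make equal safety a natural presumption. By the article's own account, acupotomy uses a 0.75 mm needle inserted 50 to 70 mm and manipulated by incision, against a 0.25 mm needle in the control arm. The Discussion also relies on excluding patients with hemostatic disorders to prevent serious events from acupotomy.

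**Working it through.** **1. The plan's own figure.** Inputs from sections 2.3 and 2.8: δ = 15, σ = 24.71, two-sided α = 5%, power 90%, 1:1 allocation, 20% dropout.

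n = 2 × [24.71 × (1.960 + 1.282) / 15]² = 57.03, rounded up to 58. Then 58 / 0.8 = 72.5, rounded up to 73.

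The stated 73 per group reproduces. It is right for VAS, and no safety quantity enters it.

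**2. No events observed.** The exact upper 95% limit for the true rate when 0 of n patients have an event is:

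- two-sided, n = 73: 1 − 0.025^(1/73) = 0.0493, or 4.9%
- one-sided, n = 73: 1 − 0.05^(1/73) = 0.0402, or 4.0%

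**3. Precision of the between-arm difference.** The article gives no adverse event rates, so the rates p below are assumptions. With the same rate in both arms, the approximate (Wald) 95% half-width is 1.96 × √[2p(1 − p)/n]. For example, at p = 0.05 and n = 73 it is 1.96 × √(0.095/73) = 0.071.

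| Assumed rate in both arms | 73 per arm | 58 per arm |
|---|---|---|
| 5% | ±7.1 points | ±7.9 points |
| 10% | ±9.7 points | ±10.9 points |
| 20% | ±13.0 points | ±14.6 points |

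The 58 column is the number expected to complete. It is a pessimistic bound for safety, since patients who leave early can still contribute adverse events.

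At 5% in both arms, the interval reaches past +5 points, so a rise from 5% to 10% is not excluded. This does not extend to doubling in general: at 10%, a doubling is +10 points, just outside ±9.7 with 73 per arm and inside ±10.9 with 58.

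**4. What a margin would imply.** The margins are also assumptions. With equal true rates and one-sided 2.5%, the power to show non-inferiority at 73 per arm is Φ(margin/SE − 1.96), where SE = √[2p(1 − p)/73].

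| Assumed margin | Rate 5% | Rate 10% | Rate 20% |
|---|---|---|---|
| 5 points | 28% | 17% | 11% |
| 10 points | 79% | 52% | 33% |
| 15 points | 99% | 86% | 62% |

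For 80% power at a 5-point margin, the number per arm before dropout would be 299, 566 or 1005 at rates of 5%, 10% or 20%. Whether 73 per arm is enough therefore depends on two quantities the article does not give.

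**The case against.** The strongest reply is that this is one sentence of expectation at the end of a Discussion. The parts of the article that say what will be done (objective, analysis, sample size) agree with one another and promise only description. No hypothesis, endpoint or decision rule hangs on the sentence. That is true and limits the weight of the point. It does not remove it: a conclusion announced in advance should be one the stated design can reach, and the Introduction repeats the theme.

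Three stronger readings are tempting, and the documents support none of them.

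- *The trial has no power to show equal safety.* Power depends on a margin and an event rate, and neither is given. With a wide margin of 15 points and rates of 10% or less, 73 per arm would give 86% or more.
- *A non-significant difference will be taken as proof of equal safety.* Section 2.8 plans no significance test on adverse events and no rule for reading one. Its chi-square and Fisher wording is attached to baseline comparisons and to categorical outcome variables, and its reach to adverse events is unclear.
- *Descriptive adverse event reporting is a mistake.* It is ordinary practice in a trial of this size.

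It can also be said that intervals for adverse event differences belong in a statistical analysis plan, which is not shown. Their absence from the article is accordingly not held against it. The recommendation below concerns what the safety statement should rest on once it is reworded.

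**Conclusion.** The point holds as a mismatch between a stated conclusion and the stated design. The Discussion expects confirmation of equal safety; the article fixes no margin or comparative safety criterion, plans descriptive frequencies and sizes the trial on VAS. As written, there is no basis for confirming the claim.

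The figures show how much uncertainty favourable-looking results would leave at this size. They rest on assumed rates and, at 5%, on a normal approximation with only about 4 expected events per arm (0.05 × 73 = 3.65), so they are rough. The zero-event limit is exact and needs no assumed rate. The primary analysis and sample size are unaffected. The change is worth making because it alters what the trial can properly conclude on safety at almost no cost.

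**What to change.** 1. **Discussion, last sentence.** Replace the expectation with a statement such as: adverse event rates will be estimated in each arm and compared descriptively; the trial is not designed to show that the two treatments are equally safe.
2. **Section 2.8, or the analysis plan if that is where such detail is kept.** Report the between-arm risk difference with an exact or score 95% confidence interval for patients with at least one adverse event, at least one treatment-related adverse event and at least one serious adverse event. State that safety will be interpreted from these intervals.

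The cost is a wording change, one added table column and a less favourable stated conclusion. Sample size, visits and data collection stay as they are.
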